#### 2.6.3. Two-Year Follow-Up (Plant B Shutdown)

After two years, there will be a three-month shutdown of Plant B due to maintenance, where its workers will be on paid leave. Directly prior to, and immediately after this shutdown, we will carry out examinations of the affected subjects. Measurements will be done in a similar manner as baseline, except from measures of cIMT and VO_2max_. At this time point, we will also monitor sleep quality and physical activity as in the one-year follow-up, and collect one-year retrospective detailed working hours from the employer’s register and do a repeated measure of respirable dust after the reopening of the plant.

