#### Shift Work Schedule and Work Content

The regular shift work schedule is a “five-shift plan”. At plant A, it consists of a five-week plan with seven night shifts, in which five are of eight h duration and two are of 12 h duration. Furthermore, the schedule includes five evening shifts lasting eight hours. As for day shifts, of which there are altogether seven, the duration is eight h on weekdays, but 12 h on weekends. The schedule for plant B is similar as to that of A when it comes to the night shift, but for plant B, only four evening shifts lasting 8 h are included. This group of workers have altogether seven day shifts, of which three are of 12 h duration and four are of 8 h duration. Both plants allow workers to take extra shifts and switch shifts between workers. All workers will have five week’s annual leave in addition to days off when changing from one type of shift to another (Table 1). Normally, workers will rotate between work tasks, consisting of supervising the production by watching computer screens, regular controls and maintenance of machines, quality control of products, and driving forklifts. For the nine months leading up to the shutdown in plant B, the work schedule will be intensified for employees at this plant as they are preparing for shutdown. Therefore, the shift work schedule will include 12-h shifts on all working days for these workers in this period, before they return to their normal shift plan after the shutdown (Table 2).

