### 2.3. Data Collection Period

Data collection is planned to start in the third quarter of 2018 and finish in the fourth quarter of 2021. All subjects will be followed for a total of three years after baseline measures, with data collection at baseline, after one year, and three years of follow-up. Furthermore, we will carry out three investigations in subgroups within the three-year study period. These investigations aim to target different important aspects of shift work and health, and will include: (1) postexaminations of subjects participating in an eight-week physical activity intervention initiated by the Occupational Health Service; (2) a five-week monitoring of sleep and physical activity of a subgroup at one-year follow-up; (3) a pre- and post-test of shift-workers, including monitoring of sleep and sleep parameters at plant B in connection to a planned three-month temporary shut-down of the plant two years after baseline. See Figure 1 for a detailed timeline of the full data collection period.

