### 2.8. Statistical Analyses

The statistical analyses will address the four research objectives stated earlier.

To elucidate the first objective, we will study the effect of shift-work on CVD-risk outcomes during a three-year follow-up using measurements at baseline and at the one- and three-year follow-ups. The primary comparison will be between the three-year follow-up and baseline. The exposure variable will be dichotomous with categories “shift-worker” and “day-worker” (reference category).

For the second research objective, we plan to use objectively measured sleep and subjectively measured sleep quality during the five-week shift period as continuous exposures variables and investigate associations to CVD risk factors. We will also include an analysis where sleep is considered a mediator between shift-work and CVD outcomes.

The third research objective concerns the effect of a three-month scheduled plant shutdown on CVD-risk outcomes. Measurements will be done before and after the shutdown, and we aim to investigate possible changes in this period.

The fourth research objective studies the effect of an eight-week HIIT intervention. We will look at the change in CVD-risk outcomes for the intervention group, and also compare this to the corresponding change for the control group. In addition to this intention to treat type analysis, we plan also to do a per-protocol analysis, where only persons having attended at least 40 percent of the training sessions will be counted as part of an HIIT group. The remaining persons will be considered to be part of the control group. We will also measure their degree of physical activity during the eight-week follow-up using the PAI index, and we will investigate whether this measure is associated with changes in the CVD-risk outcomes.

All the research questions involve longitudinal data with two or more time points. Linear and logistic mixed models will be used for all research questions. For the continuous outcomes, a linear mixed model will be used to analyze the data with a random intercept for worker, and adjustment for age, gender, and smoking. For the dichotomous outcomes, a logistic mixed model will be used with the same random-effect and fixed-effect variables. To control for multiple testing, we will use *q*-values, which is the false discovery rate equivalent for *p*-values [36].

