### Strengths and Limitation

A major strength of this study will be the comprehensive set of health measures and biomarkers used. These measures will provide in-depth information on the participating individual’s cardiovascular health, and improve knowledge on the cardiovascular health effects of shift work with night work and long working hours. The comprehensive set of biomarkers are relevant to a wide range of globally-challenging diseases, and for several of these measures, there is no or limited knowledge on their relationship to shift work.

Another strength is the controlled environment in this study, providing a detailed description of the shift organization, work hours, and sleep status of an individual level. We additionally measure factors as respirable dust exposure and physical activity, both linked to CVD risk factors [54,55], in order to gain control over other aspects which are potentially important in CVD development. This will enable us to better study effects of shift work on early manifestation of CVD.

The three-month shutdown at plant B within our study period will provide us with the opportunity to investigate whether there are any detectable changes in parameters of cardiovascular health connected to this period where participants are not exposed to shift work. In addition, the eight-week HIIT intervention carried out by the Occupational Health Service will provide great information on the effects of PA on the parameters of cardiovascular health, and additionally, will allow us to investigate the mediating effect of PA on the relationship between shift work with long working hours and CVD risk factors.

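### The uncontrolled Plant B shutdown change runs from the end of a nine-month intensified rota to the end of paid leave, but the Abstract and Discussion read it as the effect of a period without shift work

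*Protocol article*

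**What the plan says.** Section 2.3 describes the shutdown sub-study as "a pre- and post-test of shift-workers, including monitoring of sleep and sleep parameters at plant B". Section 2.6.3 sets the timing: "Directly prior to, and immediately after this shutdown, we will carry out examinations of the affected subjects". The shutdown lasts three months, starts about two years after baseline, and the workers are on paid leave.

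The section on shift work schedule and work content describes what comes before the pre-test: "For the nine months leading up to the shutdown in plant B, the work schedule will be intensified for employees at this plant". It adds that "the shift work schedule will include 12-h shifts on all working days for these workers in this period", after which workers return to the normal plan. Table 2 shows both rotas.

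Section 2.8 gives the analysis of the third objective: "Measurements will be done before and after the shutdown, and we aim to investigate possible changes in this period". It names no comparator, whereas the fourth objective has a control group. Mixed models are planned for all objectives.

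The Research Objectives section asks only whether the shutdown affects CVD-risk outcomes. The interpretation appears elsewhere. The Abstract speaks of whether stopping shift work for three months modifies early signs of CVD. Strengths and Limitation looks for changes "connected to this period where participants are not exposed to shift work". Neither place mentions the intensified rota, and it is not among the limitations.

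**The concern.** A reader of the Abstract or Discussion will take the pre-post change as what happens when people stop the shift work this study is about, which for most of the follow-up is the standard five-week plan. The starting point of the comparison is not that plan. It is a high point of the two exposures that the main objective treats as possibly harmful: long shifts and night work.

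If the intensified rota raised blood pressure or inflammatory markers, and that rise subsided during leave, the recovery would be counted in the apparent benefit of stopping shift work. A larger sample would not remove this, because it concerns what is compared and not how precisely. With one group and no comparator, season and time trend are mixed in as well.

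**Working it through.** **The plan's own figure.** No power, sample size or effect size is given for the third objective. The stated power of 0.56–0.80 concerns the first objective and does not bear on this point. The check is therefore a count of exposure, followed by an illustration of precision.

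**Standard Plant B rota, per five weeks** (schedule section and Table 1)
- Days: "altogether seven day shifts, of which three are of 12 h duration and four are of 8 h duration", so 3 × 12 + 4 × 8 = 68 h.
- Evenings: "for plant B, only four evening shifts lasting 8 h are included", so 4 × 8 = 32 h.
- Nights: 7. The text calls Plant B similar to Plant A here. Taking Plant A's durations, 5 × 8 + 2 × 12 = 64 h.
- Total: 68 + 32 + 64 = 164 h, or 32.8 h per week, in 18 shifts, of which 3 + 2 = 5 last 12 h.

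**Pre-shutdown rota, per five weeks** (Table 2, row 'Before')
- 7 days + 10 nights = 17 shifts, all of 12 h.
- Total: 17 × 12 = 204 h, or 40.8 h per week. Night-shift hours: 10 × 12 = 120.

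**Difference**
- Hours: 204/164 − 1 = +24%.
- Nights: 10/7 − 1 = +43%.
- Night-shift hours: 120/64 − 1 = +88%.
- Twelve-hour shifts: 17 against 5.

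**Sensitivity to the night-shift assumption.** If all seven standard nights lasted 8 h, the total would be 68 + 32 + 56 = 156 h. If all lasted 12 h, it would be 68 + 32 + 84 = 184 h. The excess is then 204/156 − 1 = 31% or 204/184 − 1 = 11%. The rotas differ in either case. These are scheduled hours; extra and swapped shifts are allowed.

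**Which visits fall on which rota.** If the shutdown starts at about month 24, the intensification starts at about month 24 − 9 = 15 and the plant reopens at about month 27.
- Baseline and one year: standard rota.
- Pre-test: end of intensified rota.
- Post-test: end of leave.
- Three years: standard rota, about 9 months after reopening.

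The one-year visit has no blood analyses, so blood markers have standard-rota values at baseline and three years only among these visits.

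**How easily a shift of moderate size would show up** (illustration, systolic pressure). Assumptions: 60% participation among the 55 eligible Plant B shift workers, 10–20% loss, and the within-worker SD of 7.8 from Section 2.8.2.
- n = 55 × 0.6 × 0.9 = 29.7, down to 55 × 0.6 × 0.8 = 26.4.
- SD of change = 7.8 × √2 = 11.03.
- SE = 11.03/√n = 2.02 to 2.15.
- If recovery or trend alone moved the mean by an assumed 2, 3 or 4 mmHg, the two-sided 5% test of the pre-post change would be significant with probability 0.15–0.17, 0.29–0.32 or 0.46–0.51.

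The 2–4 mmHg range is not in the documents. It only shows what such shifts would do.

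**The case against.** The strongest defence has four parts.

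- **The objective is neutral.** It concerns the effect of the shutdown, and Section 2.8 speaks of possible changes in the period. This stands. A reader might infer that the third objective itself claims an effect of stopping ordinary shift work. It does not; the over-reading is in the Abstract and in Strengths and Limitation.
- **A 12-h rota with nights is still shift work.** Leave is therefore literally a period without it, and intensified rota versus leave is a legitimate contrast for a study of long shifts. This stands too, and is why the pre-post change should be kept. It does not excuse leaving the starting point out of the interpretation.
- **The rota is disclosed and register hours are collected.** The intensification has its own table, and Section 2.6.3 collects one year of working hours, a window covering the nine months. But Section 2.8 gives these hours no role in the third objective. A fuller analysis plan may do so, and mixed models for two or more time points do not exclude the other visits. The point therefore rests on the interpretation the article states, not on missing detail.
- **Replacing the pre-post change with post-shutdown versus pooled standard-rota visits would bring its own bias.** This is right. Those visits average (0 + 1 + 3)/3 = 1.33 years, against about 2.25 for the post-test, a gap of 0.92 years. At 1.5–2 units per year, the assumed shift-versus-day difference in Section 2.8.2 used here only for scale, that is 1.4–1.8 units. Carry-over from the intensified rota could also persist at the post-test. Such a contrast needs a time term and can only be supporting.

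**Conclusion.** The point holds as one of interpretation and supporting analysis for the third objective; the primary objective is not at issue. The planned change estimates the end of the intensified rota against the end of paid leave in one group. The exposure gap from the standard rota is +24% hours, +43% nights and +88% night-shift hours, if Plant B night shifts last as long as Plant A's (+11% to +31% hours if they do not).

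The size of any bias in the outcomes cannot be obtained from the documents. A reader might infer that any improvement is over-attributed, or that the whole effect of intensification is added to the shutdown effect. Neither follows: both need the intensification to have raised the outcome, and the second also needs full reversal within three months. If the intensification had no effect, this particular bias is absent, though season, time trend and the removal of all work and dust would remain.

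**What to change.** 1. Keep the pre-post change. Label it in the Abstract, Section 2.8 and Strengths and Limitation as the change from the end of the intensified rota to the end of paid leave.
2. Add to the mixed model for the third objective the Plant B baseline, one-year (where measured) and three-year visits, with rota state (standard, intensified, leave) and a time term. Use Plant A and day-worker visits to inform the time trend where available, noting that Plant A also receives the HIIT intervention. Use the register hours to describe actual exposure.
3. Report two supporting contrasts: pre-shutdown versus standard rota (intensification), and post-shutdown versus standard rota (leave against the ordinary rota).
4. State as limitations the lack of a concurrent comparator, season, possible carry-over from the intensified rota, the removal of all work and dust during leave, and the absence of one-year blood markers.

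The cost is analysis and wording, since the visits are already planned. The supporting contrasts will have wider intervals and will depend on the time-trend assumption, most of all for blood markers. The claim that can be made becomes narrower. The work schedule itself is not in question.

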#### 2.6.4. Three-Year Follow-Up

The final data collection, identical to the one at baseline, will be carried out three years after baseline. The questionnaire will be similar to the previous ones, but will, in addition, include information on any change in lifestyle habits, such as smoking and nutrition, for the previous year.

### 2.7. Data Management

#### Data Storage

All electronic files will be placed on an encrypted database protected by two-step verification and a firewall. All physical documentation will be stored in facilities specialized for this purpose, with a physical lock. No unauthorized personnel will have access to these files or facilities.

### 2.8. Statistical Analyses

The statistical analyses will address the four research objectives stated earlier.

To elucidate the first objective, we will study the effect of shift-work on CVD-risk outcomes during a three-year follow-up using measurements at baseline and at the one- and three-year follow-ups. The primary comparison will be between the three-year follow-up and baseline. The exposure variable will be dichotomous with categories “shift-worker” and “day-worker” (reference category).

For the second research objective, we plan to use objectively measured sleep and subjectively measured sleep quality during the five-week shift period as continuous exposures variables and investigate associations to CVD risk factors. We will also include an analysis where sleep is considered a mediator between shift-work and CVD outcomes.

The third research objective concerns the effect of a three-month scheduled plant shutdown on CVD-risk outcomes. Measurements will be done before and after the shutdown, and we aim to investigate possible changes in this period.

The fourth research objective studies the effect of an eight-week HIIT intervention. We will look at the change in CVD-risk outcomes for the intervention group, and also compare this to the corresponding change for the control group. In addition to this intention to treat type analysis, we plan also to do a per-protocol analysis, where only persons having attended at least 40 percent of the training sessions will be counted as part of an HIIT group. The remaining persons will be considered to be part of the control group. We will also measure their degree of physical activity during the eight-week follow-up using the PAI index, and we will investigate whether this measure is associated with changes in the CVD-risk outcomes.

All the research questions involve longitudinal data with two or more time points. Linear and logistic mixed models will be used for all research questions. For the continuous outcomes, a linear mixed model will be used to analyze the data with a random intercept for worker, and adjustment for age, gender, and smoking. For the dichotomous outcomes, a logistic mixed model will be used with the same random-effect and fixed-effect variables. To control for multiple testing, we will use *q*-values, which is the false discovery rate equivalent for *p*-values [36].

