### 2.5. Physical Activity Intervention

The PA intervention will be carried out by the local Occupational Health Service, with support from Kristiania University College, School of Health Science. The intervention group will consist of all volunteering shift workers in plant A (out of 51 eligible workers), while a control group of shift workers will be recruited from plant B (out of 55 eligible workers). Subjects in the intervention group will perform three supervised training sessions per week for eight weeks. Training sessions will be carried out on a work site in the enterprise’s own training facilities, and will be guided by a physical therapist. Based on participant’s own choice, sessions will be performed by cycle ergometer, row machine, steep hill walking, or running. Dedicated motivators will log all performed sessions during the eight-week intervention period, and will afterwards continue to motivate coworkers to undertake regular PA during the three-year follow-up. The motivators will have regular meetings with the project leaders throughout the follow-up period. The total duration of an interval session will be 17 min, including 10 min warm-up and 3 min cool-down at 60–70% maximal heart rate (HRmax) [29]. During warm-up, participants should not experience any shortness of breath, and ideally, should rate their perceived exertion to be 11–13 on a Borg scale [30]. In extension of the warm-up, the subject will carry out a single four-minute interval at 85–95% of HRmax, rating 16–19 on Borg scale. Subjects will be instructed to strive to attain the desirable HR range within the two first minutes of the four-minute effort. All subjects will be equipped with a personal heart rate measurement device that includes Personalized Activity Intelligence (PAI), in which a high level of PAI seems to prevent or postpone CVD [31,32].

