#### 2.8.1. Loss to Follow-Up, Compliance, and Missing Data

Based on previous experiences, we expect approximately 60% of the total workforce at the plants to volunteer for participation in the project. The project will be deeply anchored with the plant’s leadership. Participants will be closely followed by the Occupational Health Service after inclusion, and we expect 10–20% loss to follow-up for the whole 3-year period. For the intervention group, 80–90% compliance is expected for the planned and supervised sessions. Outcome will be censored in case of people leaving the employment at the plants due to unemployment, disability pension, or rehabilitate pension. Missing outcome values will be taken into account by the mixed model approach, and no prior imputation is necessary. For the adjustment variables, we do not expect much missingness.

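### The analysis called per-protocol for the HIIT objective is an as-treated regrouping that counts low-attending Plant A volunteers as controls

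*Protocol article*

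**What the plan says.** Section 2.5 of the protocol article draws the intervention group from shift workers at Plant A who volunteer (51 eligible) and the control group from shift workers at Plant B (55 eligible). Allocation is by plant and willingness, not by randomisation. The programme is "three supervised training sessions per week for eight weeks".

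Section 2.8 first compares the change in CVD-risk outcomes between these two groups as formed. It then continues: "In addition to this intention to treat type analysis, we plan also to do a per-protocol analysis". In that second analysis, "only persons having attended at least 40 percent of the training sessions will be counted as part of an HIIT group", and "The remaining persons will be considered to be part of the control group".

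The models in section 2.8 adjust for age, gender and smoking. No term for plant or for predictors of attendance is named. Section 2.8.1 states that "80–90% compliance is expected for the planned and supervised sessions" in the intervention group.

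**The concern.** A per-protocol analysis restricts the data to people who followed the plan for the group they were in. Those who did not are left out. Section 2.8 instead sends low attenders to the other group on the basis of what they did after baseline. That is an as-treated regrouping, and the label tells the reader something else.

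The moved workers differ from the planned controls in three ways: they volunteered for training, they may have done part of it, and they work at the other plant, on a different shift plan (section 2.1, Table 1). Two distortions follow. Any training effect they obtained enters the control mean and pulls the contrast toward zero. In addition, if low attenders would have changed differently from Plant B workers for reasons unrelated to HIIT, that difference enters the comparator too, in either direction.

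What is at stake is the interpretation of this one analysis. If its result differs from the intention-to-treat type result, the reader cannot tell how much comes from training and how much from relabelling.

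**Working it through.** The article gives no figure for this analysis to reproduce. The check sizes the effect of the rule.

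**Inputs from the article.** Three sessions a week for eight weeks, and the 40% threshold (sections 2.5, 2.8); 51 and 55 eligible workers (section 2.5); expected compliance 80–90% and project participation about 60% (section 2.8.1).

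**Assumptions.** The 60% applies equally to HIIT uptake and control recruitment (the article does not give these separately). The effect is linear in sessions attended.

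**Who is moved.** 3 × 8 = 24 sessions; 0.40 × 24 = 9.6. At least 10 sessions are needed to stay in the HIIT group, so workers with 0–9 are moved. The most a moved worker can have done is 9/24 = 37.5% of the programme.

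**Group sizes.** 0.6 × 51 = 30.6, about 31 volunteers; 0.6 × 55 = 33 controls.

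**Formulas.** Let *m* be the number moved. Moved workers make up *m*/(*m* + 33) of the comparator. The largest dilution, as a share of the effect of the full 24-session programme, is 0.375 × *m*/(*m* + 33).

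**How many are moved.** The article does not say whether 80–90% is a share of workers or a mean attendance, so both readings are shown.

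- *Share of workers who comply.* If the 10–20% who do not comply all fall below the threshold, 3 to 6 of 31 are moved.
- *Mean attendance.* The largest possible share at 9/24 arises when everyone else attends every session: (1 − mean)/(1 − 0.375). This gives 0.10/0.625 = 16% at a mean of 90%, about 5 workers, and 0.20/0.625 = 32% at a mean of 80%, about 10 workers.

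| Reading | Moved | Share of comparator | Largest dilution |
|---|---|---|---|
| 10% of volunteers | 3 | 3/36 = 8.3% | 0.375 × 3/36 = 3.1% |
| 20% of volunteers | 6 | 6/39 = 15.4% | 0.375 × 6/39 = 5.8% |
| Mean 90%, worst case | 5 | 5/38 = 13.2% | 0.375 × 5/38 = 4.9% |
| Mean 80%, worst case | 10 | 10/43 = 23.3% | 0.375 × 10/43 = 8.7% |

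The smallest dilution is zero, when the moved workers attended nothing. Measured against a HIIT group that itself averages 80% attendance (0.8 × 24 = 19.2 sessions), the ratio is 9/19.2 = 0.469. The first two rows then become 0.469 × 3/36 = 3.9% and 0.469 × 6/39 = 7.2%, still within the last row.

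**Selection.** Each unit by which the moved workers' underlying change differs from that of Plant B controls shifts the comparator mean by *m*/(*m* + 33) units: 0.08 for 3 workers, 0.15 for 6, 0.23 for 10. The article gives neither the size nor the sign of that difference.

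**The case against.** The strongest reply has three parts.

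First, the rule touches only a supplementary analysis. The intention-to-treat type comparison keeps the Plant A and Plant B groups as formed, HIIT is the fourth of four objectives, and section 2.8.2 treats the first as primary. This stands, and it limits the severity. A reader might infer that the main HIIT result is compromised; the article does not support that.

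Second, few workers may be moved. This also stands in part. A reader might picture 40% of volunteers below the line, or moved workers keeping half the effect. If 40% were below it, mean attendance could not exceed 0.60 + 0.40 × 0.375 = 75%, which is under the 80–90% expected. Half the full-programme effect exceeds the 37.5% maximum under a linear dose effect. A reader might also infer that the rule flatters HIIT because low attenders are ill, unfit or overworked. The article gives no reasons for low attendance, so no direction or size in mmHg can be assigned. Small expected numbers do not justify the rule, however: it matters most when attendance disappoints, which is when such an analysis would be consulted.

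Third, excluding low attenders also selects on post-baseline behaviour, and the HIIT group is the same people under either rule. This is correct. Suppose volunteers as a whole match Plant B in underlying change and low attenders differ by one unit. The retained attenders then differ the other way by 3/28 = 0.11 units (3 moved) or 6/25 = 0.24 units (6 moved). That exceeds the 0.08 and 0.15 units that exclusion takes out of the comparator, and it remains. Exclusion also makes plant and treatment coincide fully in this analysis. So exclusion does not cure selection; it removes the contamination of the control group and makes the label true.

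**Conclusion.** The point holds as a moderate fault in a secondary analysis. The analysis named per-protocol is an as-treated regrouping, and its comparator includes volunteers from the other plant with up to 9 of 24 sessions. Because the article states the rule outright, this is not a detail left to an analysis plan.

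With 31 volunteers, 33 controls and a linear dose effect, moving 10–20% of volunteers makes about 8–15% of the comparator HIIT volunteers and dilutes the contrast by at most about 3–6%. About 9% is the ceiling if mean attendance is 80% and as many as possible sit at 9 of 24. These figures rest on the assumed HIIT uptake and on linearity. Selection can add bias of unknown sign that the article does not allow to be sized. The intention-to-treat type result is not affected.

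**What to change.** In section 2.8, replace the sentence that assigns the remaining persons to the control group. Suggested wording: *Intervention-group workers who attended fewer than 40% of sessions (fewer than 10 of 24) are excluded from the per-protocol set; the comparator is the Plant B control group only.*

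If the regrouped analysis is kept, call it as-treated and report it as a sensitivity analysis next to the other two.

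Add one sentence stating that exclusion removes the contamination of the control group, but not the self-selection of adherers or the confounding by plant. The planned PAI analysis can stay as it is and already gives a dose-type view.

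The cost is a few workers in this analysis only. With 3–6 excluded, the comparison is 28 against 33 or 25 against 33, in place of 28 against 36 or 25 against 39. No data collection changes.
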